## Procedure

Clinician and patient participants will be identified through research staff presentations at team meetings, clinics, training events and following email and telephone contact with staff.

Clinician participants will be approached by a research assistant and patient participants by their lead clinician. All interested potential participants will be provided with the study information sheet and will have the opportunity to discuss the study in a meeting or telephone conversation with a research assistant who is trained in taking informed consent and in Good Clinical Practice. Following informed consent, participants will complete the basic demographic information and baseline questionnaire measures. They will then be randomised to either the intervention or comparison condition. The intervention or comparison condition will be provided according to a manualised protocol as part of a single session lasting up to 1 h, after which participants will also complete the same questionnaires in the post-intervention assessment in the same session.

Participants in the intervention condition will be provided with access to the online intervention for the subsequent month. Where a patient participant does not have access to a computer, they will be provided with an iPad, locked to the intervention site, to enable access in the subsequent month. Usage data will be tracked through Google Analytics and will be stored safely and confidentially; data willonly be accessible to the researchers via a password. Usage data will be stored in an encoded format that prevents tampering. Comparison participants will be provided with the NHS choices website link and handout. This website is publicly available. After one month (− 2/+ 8 weeks), each participant will complete the same questionnaires in a follow-up assessment, which will be conducted by a research assistant who is blind to randomisation arm, in person or by telephone. All participants in the intervention arm will also complete a brief feedback questionnaire on their use of the intervention.

A small subsample of six patients and six clinicians who receive the informed choice intervention materials will also undertake a brief semi-structured interview with a research assistant to explore their experience of using the intervention materials and to provide feedback to further refine the intervention.

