**Methods:**

The design is a two-arm, feasibility randomised controlled trial (RCT), with 1:1 randomisation, stratified by participant group and site. Participants are 40 psychosis patients and 40 clinicians, who are ambivalent towards uptake or implementation of CBTp. Sites are community and inpatient services in Sussex and London. The intervention is a pre-CBT digital psychoeducation intervention designed to address identified knowledge and attitudinal barriers to uptake and implementation of CBTp, incorporating behaviour change mechanisms, and supported by animated introductory, patient and clinician stories. The comparator is the NHS choices website for CBT. The primary aim is to assess clinical feasibility (recruitment, randomisation, acceptability, use, delivery, outcome measurement, retention). A secondary aim is a preliminary evaluation of efficacy. Outcomes will be assessed at baseline, post intervention, and one-month follow-up (blind to treatment arm). The primary efficacy outcome is likelihood of offering/taking up CBTp. Secondary outcomes include knowledge and attitudes towards CBTp, illness perceptions, empowerment, psychological wellbeing (patients only) and CBTp implementation (clinicians only). Use of the intervention and CBT behaviours during the follow-up period will be recorded and captured in a feedback questionnaire. Use, acceptability and experience of outcome assessment will be explored in qualitative interviews with participants (*n* = 6 per group). The efficacy evaluation will report descriptive data, key model parameters and 95% highest probability density intervals in a Bayesian growth model.

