## Method

### Design

The design is a two-arm, multicentre, longitudinal, feasibility RCT, with 1:1 block randomisation and varying block size, stratified by participant group (clinician or patient) and site (London or Sussex). Participants will be randomised by Kings College London Clinical Trials Unit, independently from the trial team, using an online randomisation system. Randomisation will be initiated by the research assistant immediately after the baseline assessment and before intervention delivery. Allocation will be confirmed by email. Baseline and one-month follow-up data will be collected blind to allocation to ensure unbiased data collection. Post-intervention data will not be collected blind to allocation as these data are collected in a single session, immediately after intervention delivery. Participants will not be blind and will be reminded of the blind procedure at the start of the one-month follow-up, in order to reduce the risk that they reveal their allocation, and blind breaks will be recorded. For reporting the feasibility of the RCT, the CONSORT (Consolidated Standards of Reporting Trials; http://www.consort-statement.org/) extension to randomised pilot and feasibility trials statement will be followed [54]. For the protocol, the SPIRIT (Standard Protocol Items: Recommendations for Interventional Trials) Figure and Checklist are provided in this paper see: Fig. 1 and Additional file 1.

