### Primary feasibility outcomes

The primary purpose is to assess the feasibility of the interventions in terms of acceptability, usability and accessibility, and to examine the feasibility of methods of a future trial including measures, recruitment procedures and trial processes. This will be done through monitoring using the study CONSORT diagram, through system analytics on use of the digital intervention during the one-month period, through the user feedback questionnaire collected at the end of one month, and through a qualitative interview with a sub-sample of those receiving the intervention (*n* = 6 per group) at the end of one month. The primary feasibility outcomes are:Feasibility of eligibility criteria, recruitment and retention within the NHS (numbers referred, recruited, consented, randomised and retained in the trial) during the trial recruitment period of August 2017 to May 2018;Feasibility of use, accessibility and acceptability of the intervention and the outcome measures in the NHS, measured using feedback questionnaire responses regarding use of the intervention; activity data on use of the intervention during the follow-up period (average number of pages visited per participant), qualitative interviews with six patients and six clinicians (three each in Sussex and London) regarding their experience of using the intervention, the selection of outcome measures and participation in the trial; September 2017 to May 2018.

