### Efficacy evaluation outcomes

Participants will complete the following measures at (1) baseline, (2) immediately after introduction to the intervention, and (3) at one-month follow-up.Likelihood of offering/referring or taking up CBT will be measured using a single Likert scale (0–10) for how likely the participant is, in general, to offer/refer psychosis patients for CBT, if this were available, or how likely the participant is to take up CBTp if it were offered today, each rated from not at all (0) to extremely likely (10);Knowledge and attitudes towards CBTp will be measured using mean factor score for two new questionnaires developed during earlier phases of the current study. The clinician questionnaire comprises 27 items, which form three factors (pro CBT content, supportive CBT culture, confidence in the value of CBT to patients), all with high internal consistency (α = 0.87, 0.82 and 0.71, respectively) and predictive validity for likelihood of referring/offering CBTp (robust estimate of correlation = 0.45, 0.53 and 0.32, respectively). The patient questionnaire comprises 35 items, which form four factors (positive attitudes towards CBTp, personal barriers, doubt regarding efficacy and fear related to CBTp), each with good internal consistency (α = 0.94, 0.83, 0.76 and 0.82, respectively) and predictive validity (robust estimate of correlation = 0.50, 0.46 and 0.54, respectively), except fear which was not a good predictor of uptake (robust estimate of correlation = 0.26). In each questionnaire, items are scored on a 7-point Likert scale from disagree strongly to agree strongly;Illness perceptions will be measured using the mean factor scores for the modified illness perceptions questionnaire [55] which has good internal consistency (α = 0.70) and forms three factors (cure/control, timeline, causes). The cure/control and timeline factors have good internal reliability and test–retest reliability (cure/control α = 0.09/0.09 and timeline α = 0.7/0.06). Individual items are scored on a 5-point Likert scale from strongly agree to strongly disagree;Attitudes and behaviours towards CBTp implementation will be measured using mean scores for five constructs of the NOMAD tool [56] adapted for CBTp implementation (clinicians only). The tool includes three items that assess normalisation of CBTp on a 0–10 Likert scale from ‘still feels very new’ to ‘feels completely familiar’, and 20 items that assess the four core constructs of coherence of CBTp with standard care, cognitive participation, collective action and reflexive monitoring, each rated on a 5-point Likert scale from strongly agree to strongly disagree;Psychological wellbeing will be measured using the CHOICE short-form measure of psychological wellbeing (patients only). This scale has been produced by our research group and has good psychometric properties including internal consistency (α = 0.83), test–retest reliability (ICC = 0.73), convergent validity (*r* = 0.52 with quality of life; − 0.58 with mood) and sensitivity to change (*t* = − 0.41) [57]. The short form used in the current study has been widely used including in the national IAPT-SMI pilot sites in the UK [30], and includes 11 items, and one personal goal item, each rated on a 0–10 Likert scale from ‘worst’ to ‘best’. The total mean score will be used;Empowerment will be measured using the mean factor scores for the Rogers’ Empowerment scale (patients only) [58] which has good internal consistency (α = 0.82) and factor structure with five factors: self-esteem (α = 0.82); perceived power (α = 0.59); optimism and control over the future (α = 0.45); community activism/autonomy (α = 0.59); and righteous anger (α = 0.64), with good convergent (hope/recovery *r* = 0.67, empowerment *r* = 0.45) and predictive validity (psychosis symptoms *r* = − 0.39). The scale includes 28 items measured on a 4-point Likert scale from strongly agree to strongly disagree;CBT-related activities in the preceding month will be based on interview and case notes screen (at one-month follow-up).

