
The interview regarding CBT-related activities is part of a larger interview to explore attitudes to and use of the intervention during the follow-up period. The whole interview takes approximately 10 min.

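### The one-month CBT-activity interview, as described, is likely to disclose the arm to an assessor who is meant to be blind

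*Protocol article*

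**What the plan says.** All references are to the protocol article.

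- **Design** makes the general promise: "Baseline and one-month follow-up data will be collected blind to allocation to ensure unbiased data collection". It exempts the post-intervention assessment, because that takes place in the same session as delivery. It exempts no one-month outcome. Participants know their arm and are reminded of the blind procedure at the start of follow-up "in order to reduce the risk that they reveal their allocation, and blind breaks will be recorded".
- **Procedure** describes a follow-up assessment "which will be conducted by a research assistant who is blind to randomisation arm, in person or by telephone". The next sentence adds the form for one arm: "All participants in the intervention arm will also complete a brief feedback questionnaire on their use of the intervention".
- **Primary feasibility outcomes** dates that form: use and acceptability are studied, among other routes, "through the user feedback questionnaire collected at the end of one month".
- **Efficacy evaluation outcomes** lists CBT-related activity and names its sources: "CBT-related activities in the preceding month will be based on interview and case notes screen (at one-month follow-up"). It then adds: "The interview regarding CBT-related activities is part of a larger interview to explore attitudes to and use of the intervention during the follow-up period".
- The **Abstract** (Methods paragraph) names a different source: "Use of the intervention and CBT behaviours during the follow-up period will be recorded and captured in a feedback questionnaire".

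**The concern.** An assessor cannot easily explore how someone used a website without learning which website it was. If the CBT-activity questions sit within that conversation, the person recording the answers is likely to know the arm. CBT-related activity is then open to assessor influence in how far answers are probed and how they are coded.

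Two things are at stake. One is the comparability of the two arms on an outcome that records what participants did about CBT in the preceding month. The other is the feasibility information. Trial processes and outcome measures are what this trial sets out to test, and the record of blind breaks should help to show whether a blinded follow-up can be achieved. If the follow-up procedure itself produces breaks, that record says less about the question it is meant to answer.

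**Working it through.** There is no figure in the protocol to reproduce. The check sets the statements side by side.

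**1. Scope of the blinding.** Design covers one-month data as a whole and names only the post-intervention assessment as unblinded. CBT-related activity is a one-month measure under Efficacy evaluation outcomes, so it falls under the promise.

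**2. Content of the interview.** That section states that the CBT-activity questions form part of a longer interview on participants' views and use of the intervention. The protocol uses the word *intervention* in two ways, so both readings need testing.

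- *Narrow reading (the informed-choice website only).* Either the use questions go to one arm only, which identifies it, or they go to both and comparator participants have nothing to report. The arm is disclosed either way.
- *Broad reading (whichever website was shown).* The question is neutral, but the answer need not be. One site has animated stories, a goals section and a route map; the other is written text on a public NHS page. Describing use of either invites disclosure.

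Disclosure is likely on both readings. The order of questions within the interview is not stated. If the CBT-activity items came first, those answers would be obtained before any disclosure, but nothing secures that order.

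**3. The feedback form.** It goes to one arm and is due at the end of one month, when the blind assessment takes place. The protocol does not say who gives it or when. The consequence differs by case:

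| How the form is given | Effect on other one-month data |
|---|---|
| By the blind assistant, before the scales or interview | Arm known while they are collected |
| By the blind assistant, after everything else | Nothing collected earlier is affected |
| Self-completed and returned unseen, or by another person | None |

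The text therefore supports a conflict for the CBT-activity interview, and only a possibility for the other scales.

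**4. The safeguards.** A reminder to participants guards against spontaneous disclosure. It does little when the assessor's own questions call for the information. Recording breaks measures the problem but does not prevent it.

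**5. Source of the CBT-activity data.** The Abstract says the feedback questionnaire captures CBT behaviours, and Procedure gives that questionnaire to the intervention arm. Efficacy evaluation outcomes names interview and case notes and limits them to neither arm. The fuller statement gives the comparator arm a data source, so the Abstract sentence is the one out of line.

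**6. How many participants are involved.** The target is 40 patients + 40 clinicians = 80. At 1:1 allocation, 80 / 2 = 40 would be due the feedback form. CBT-activity interviews would number from 0.80 × 80 = 64 (at the 80% retention benchmark) to 80 (full retention). These are counts of visits at which the procedure applies, not estimates of how often the blind would fail. The protocol gives nothing from which to compute a failure rate or a bias.

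**The case against.** The strongest reply is that this is loose wording in a condensed article. The feedback form stands in its own sentence with no administrator or order attached, and a self-completed form given last would be harmless. The article refers readers to its SPIRIT figure for visit details; that figure is not available here, and staffing and order are commonly left to the full protocol. The word *intervention* is also used for both arms in places, for example where Efficacy evaluation outcomes has participants complete measures immediately after being introduced to it. Case notes are a second source that does not depend on the interview. The likelihood rating, which is the primary efficacy outcome, and the other scales are self-reported by unblinded participants, so assessor blinding protects them little. CBTp-related behaviour is reported descriptively, no significance tests are planned, and the protocol is examined after 10 participants per group.

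Much of this stands, and it limits the point. It does not remove it. The difficulty is not an omitted detail: the article states that one-month data are collected blind and also states what the interview contains, and the two do not fit together. The broad meaning of *intervention* softens the conflict without resolving it. The early examination could catch the problem, but it is described as a general check on intervention and protocol, with no stated attention to blinding.

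Three stronger readings may tempt a reader, and the document supports none of them:

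- *Blinding at one month fails almost completely.* That requires the same assistant to give the arm-specific form before or during the other measures, which is nowhere stated.
- *The comparator arm has no CBT-activity data.* Efficacy evaluation outcomes restricts the interview and case-note screen to neither arm.
- *CBT-related activity is the only behavioural outcome.* The adapted NOMAD tool is described as covering clinicians' attitudes and behaviours towards implementation.

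**Conclusion.** The point holds in a limited form. As written, the interview that yields CBT-related activity is likely to reveal the arm to an assessor who is supposed not to know it, and the recorded blind breaks would partly reflect the procedure. For the remaining one-month scales the effect is only inferred.

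The size is moderate. One secondary outcome, reported descriptively and partly backed by case notes, is affected, together with the blind-break data as feasibility evidence. The primary efficacy outcome is little touched. The conclusion assumes that the blind assistant who conducts the follow-up also conducts this interview, which is the natural reading of Design and Procedure, and that no order or arm-neutral wording is fixed elsewhere. If the unseen figure or a full protocol already fixes them, what remains is a correction to the article's text.

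It deserves attention because Analysis plan foresees that a later trial would keep to this protocol if it does not change, so the conflict would carry over.

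**What to change.** 1. In Procedure, fix the order of the one-month visit. In both arms the blind assessor completes all scales, an identically worded CBT-activity interview and the case-note screen, before any question about use of either website.
2. Collect use and feedback items only after that, either self-completed or through the assistant who delivered the session and so already knows the arm.
3. If this separation cannot be made, state in Design that CBT-related activity is not assessed blind.
4. Record whether each blind break happened before or after the CBT-activity items, so that the feasibility report can separate breaks caused by the procedure from the rest.
5. Align the Abstract with Efficacy evaluation outcomes: CBT-related activity comes from interview and case notes in both arms, and the feedback form covers use of the intervention.

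The cost is a reordered visit, a form edit and a few sentences, with existing staff and no additional participants. If follow-up visits have begun, the team should record the date of the change and say whether it counts as a protocol change, because Analysis plan makes the Bayesian growth model conditional on an unchanged protocol. If practice already follows this order, only the text needs correcting.

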### Analysis plan

Descriptive data will be used to report referrals, recruitment, retention, use of the intervention and CBTp-related behaviour. Audio-recorded qualitative interviews will be transcribed and themes will be extracted using Interpretative Thematic Analysis. Themes will be translated into recommendations for refining the intervention, trial procedures, outcome measures and protocol in preparation for a future RCT, if feasibility and preliminary efficacy data are promising. There will be a preliminary examination of the data after 10 participants per group have been recruited. If, at that stage, the intervention and protocol are regarded as sound and needing no significant refinement, the study will proceed to recruit the full 40 participants per group. If there is need for further refinement, the study will allow for successive refinement of the protocol with the next 10 participants per group until the trial team are satisfied that the final protocol is optimal. If the protocol changes during data collection descriptive statistics will be reported (where feasible) by timepoints at which protocol changes were made. These will not be used to inform a subsequent trial, but only to describe what happened in the current trial. If the protocol does not change during data collection and, therefore, a subsequent trial would adhere to the current protocol, descriptive statistics will be reported; a Bayesian growth model will also be fit to the data, blind to study arm, treating change over time as a random effect within participants and randomisation arm as a time-invariant fixed effect. 95% highest probability density (HPD) intervals will be used to estimate plausible values of the key model parameters (notably the parameter quantifying the difference between the arms in the rate of change of the likelihood of taking up/referring to CBT). Bayesian growth model parameters are estimated using an iterative process (Markov chain Monte Carlo [MCMC]) and missing values are estimated as unknown parameters [59] in a process akin to multiple imputation [60]. To check the influence of priors of the model estimates, model fit with both informative and uninformative priors will be compared.

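### The efficacy parameter singled out is an arm difference in rate of change; with two readings either side of one session and a third at about one month, the arm difference at one month would be clearer

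*Protocol article*

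**What the plan says.** The protocol article, under Analysis plan, fits a Bayesian growth model if the protocol has not changed during data collection. It describes the model as "treating change over time as a random effect within participants and randomisation arm as a time-invariant fixed effect". Intervals of 95% highest probability density are to be given for the key parameters, and the one singled out is "the parameter quantifying the difference between the arms in the rate of change of the likelihood of taking up/referring to CBT". No between-arm contrast at a given visit is named. The text does not say that growth is linear, whether time means elapsed time or visit number, or whether the arms share a baseline intercept.

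Timing comes from three other places:

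- **Efficacy evaluation outcomes:** the measures are taken at baseline, "immediately after introduction to the intervention, and (3) at one-month follow-up".
- **Design:** "Randomisation will be initiated by the research assistant immediately after the baseline assessment and before intervention delivery". The post-intervention readings are not collected blind, because "these data are collected in a single session, immediately after intervention delivery". The one-month reading is collected blind to allocation.
- **Procedure:** after a session of up to 1 h, "participants will also complete the same questionnaires in the post-intervention assessment in the same session". Follow-up is timed as "After one month (− 2/+ 8 weeks").

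Under Aims and objectives, the other efficacy summary is descriptive: mean changes over time within each arm.

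**The concern.** A rate of change summarises an effect well when it builds up roughly in proportion to time. Here two of the three readings appear to sit at almost the same moment, one just before and one just after the main exposure. Any effect of the session itself is then a jump between two readings that share a time point, and a single slope cannot represent a jump. Part of the benefit goes into the level of the line and is lost from the slope, or the post-session reading is ignored, depending on how time is coded.

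Aims and objectives says that the trial should supply the parameters needed to design a future trial, and the Analysis plan makes preparation for that trial depend partly on promising efficacy data. Required sample size varies with the inverse square of the effect. If a halved effect were carried into planning, the size would be multiplied by 1/0.5² = 4. A slope near zero could also make a lasting benefit look like none.

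**Working it through.** The article gives no effect size, SD or correlation, so there is no stated figure to reproduce.

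**Inputs.** Let D1, D2 and D3 be the expected arm differences at baseline, post-session and one month. Randomisation gives D1 = 0. Assume an immediate benefit D2 = d, of which a fraction f remains at one month, so D3 = f·d. All results scale with d.

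**Case A: linear in elapsed time, separate arm intercepts.** Times are 0, 0 and T. For complete data at common times, the least-squares slope is also the mixed-model slope, with or without random slopes:

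slope × T = D3 − (D1 + D2)/2 = (f − 0.5)d

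**Case B: elapsed time, common baseline intercept.** Take random intercepts and uncorrelated random slopes, and let ρ be the correlation between the two same-day readings. The weighted estimate is

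slope × T = [f − ρ/(1 + ρ)]d

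ρ is not given. Illustrative values of 1/2 and 2/3 give f − 0.33 and f − 0.40. At ρ = 0 the slope recovers f·d, and as ρ approaches 1 it returns to Case A.

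**Case C: visits coded 0, 1, 2, separate arm intercepts.** Slope per step = (D3 − D1)/2 = f·d/2, so over two steps it is f·d. D2 does not enter.

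| Benefit at one month | True difference | A, over the month | B, over the month | C, per step | C, two steps |
|---|---|---|---|---|---|
| Sustained (f = 1) | d | 0.50d | 0.60d to 0.67d | 0.50d | d |
| Half faded (f = 0.5) | 0.50d | 0 | 0.10d to 0.17d | 0.25d | 0.50d |
| Three-quarters faded (f = 0.25) | 0.25d | −0.25d | −0.15d to −0.08d | 0.125d | 0.25d |
| Fully faded (f = 0) | 0 | −0.50d | −0.40d to −0.33d | 0 | 0 |

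**Follow-up window.** Taking one month as about four weeks, the window runs from 2 to 12 weeks. At 30.4 days per month, that is 14/30.4 = 0.46 to 84/30.4 = 2.76 months. In Case A a sustained benefit has a slope of 0.5d/T per month: 0.5/0.46 = 1.09d if everyone is seen at 2 weeks, and 0.5/2.76 = 0.18d if everyone is seen at 12 weeks. With visits spread evenly over the window it is about 0.30d, varying somewhat with the assumed variances. The same benefit therefore gives different rates according to visit scheduling.

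**If baseline came earlier.** The same day is implied, not stated. With baseline one week before the session (times 0, 0.23 and 1.23 months) and separate intercepts, a sustained benefit gives 0.57d per month, or 0.57 × 1.23 = 0.70d over the period. A fully faded one gives −0.30d per month. The distortion shrinks but does not vanish.

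**Direct contrast.** With visit as a category, the one-month arm difference has expectation f·d in every row, whatever the time coding.

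**The case against.** The strongest reply is that a reader might infer that the plan will halve a sustained benefit and report a fading one as nil or as harm. The document does not support that as a flat statement. It fixes neither linearity nor time coding, details that an analysis plan not shown here may settle. With visit coding and separate intercepts, the two-step change is exactly the one-month difference. Even in Case A, zero needs a 50% fade and a negative value needs more. In Case A the fitted one-month difference, intercept plus slope, is also correct: for a sustained benefit, 0.5d + 0.5d = d. The error comes from reading the slope alone. All of this stands, and it makes the point conditional.

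The effect need not be a pure step either. The first session is introductory and access continues for the month (Intervention; Procedure), so ratings may go on rising. That is fair, but it does not rescue the slope: in Case A, D3 − D2/2 still subtracts half of any immediate gain.

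A reader might also infer from the description of arm as time-invariant that the model cannot yield a difference in change at all. That reading fails. The words describe a covariate that does not vary by visit, and the parameter named next requires an arm-by-time term.

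The blinding contrast is limited. Participants know their arm at both later visits and rate themselves, so only assessor blinding differs. The 1.09d and 0.18d figures are extremes of the window. Lastly, efficacy is a secondary aim, no significance tests are planned, the numerical progression benchmarks concern recruitment and retention, and descriptive means over time would show a step or a fade.

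**Conclusion.** The point holds in conditional form. The article singles out one difference in rate of change for a set of visits that suits it poorly, and names no between-arm difference at one month. Under a linear model in elapsed time with separate arm intercepts, the slope contrast over the month is (f − 0.5)d: half of a sustained benefit, zero at a 50% fade, and negative beyond that. With a common baseline intercept and same-day correlations of 1/2 to 2/3, a sustained benefit shows as 0.67d to 0.60d. With visit coding the two-step change is right, but the rate per step is half of it and the post-session data do not contribute.

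These figures assume no baseline difference, complete data, baseline on the day of the session, and an immediate effect d whose size the documents do not give. The rating is should-fix and no higher, because the analysis is secondary, has no significance test, and is fitted only if the protocol stays unchanged.

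**What to change.** In the Analysis plan, keep the Bayesian model and the participant random effects, but treat visit as a three-level factor with arm-by-visit terms. Constrain the baseline mean to be equal across arms, or use baseline as a covariate. Name the between-arm difference in likelihood rating at the assessor-blind one-month visit as the key parameter, with its 95% HPD interval. Report the post-session difference, which is not collected blind, as a separate short-term estimate. The planned comparison of informative and uninformative priors would then apply to these two differences.

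The cost is about a sentence in the plan and one extra parameter: three visit means plus two arm differences make five mean parameters, against four for a linear model with an intercept and a slope in each arm. No new data are needed.
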